# NA-CONTROL: a study protocol for a randomised controlled trial to compare specific outpatient rehabilitation that targets cerebral mechanisms through relearning motor control and uses self-management strategies to improve functional capability of the upper extremity, to usual care in patients with neuralgic amyotrophy

**DOI:** 10.1186/s13063-019-3556-4

**Published:** 2019-08-07

**Keywords:** Neuralgic amyotrophy, Parsonage Turner syndrome, Neurorehabilitation, Upper extremity, Scapular dyskinesia, Motor control, Peripheral nerve dysfunction, Maladaptive neuroplasticity, Physical therapy, Occupational therapy

## Abstract

**Background:**

Neuralgic amyotrophy (NA) is a distinct peripheral neurological disorder of the brachial plexus with a yearly incidence of 1/1000, which is characterised by acute severe upper extremity pain. Weakness of the stabilising shoulder muscles in the acute phase leads to compensatory strategies and abnormal motor control of the shoulder - scapular dyskinesia. Despite peripheral nerve recovery, scapular dyskinesia often persists, leading to debilitating residual complaints including pain and fatigue. Evidence suggests that persistent scapular dyskinesia in NA may result from maladaptive cerebral neuroplasticity, altering motor planning. Currently there is no proven effective causative treatment for the residual symptoms in NA. Moreover, the role of cerebral mechanisms in persistent scapular dyskinesia remains unclear.

**Methods:**

NA-CONTROL is a single-centre, randomised controlled trial comparing specific rehabilitation to usual care in NA. The rehabilitation programme combines relearning of motor control, targeting cerebral mechanisms, with self-management strategies. Fifty patients will be included. Patients are recruited through the Radboud university medical center Nijmegen, the Netherlands. Patients with a (suspected) diagnosis of NA, with lateralized symptoms and scapular dyskinesia in the right upper extremity, who are 18 years or older and not in the acute phase can be included. The primary outcome is the Shoulder Rating Questionnaire score, which measures functional capability of the upper extremity. Secondary clinical outcomes include measures of pain, fatigue, participation, reachable workspace, muscle strength and quality of life. In addition, motor planning is assessed with first-person motor imagery and functional magnetic resonance imaging. In a sub-study the patients are compared to 25 healthy participants, to determine the involvement of cerebral mechanisms. This will enable interpretation of cerebral changes associated with the rehabilitation programme and functional impairments in NA.

**Discussion:**

NA-CONTROL is the first randomised trial to investigate the effect of specific rehabilitation on residual complaints in NA. It also is the first study into the cerebral mechanisms that might underlie persistent scapular dyskinesia in NA. It thus may aid the further development of mechanism-based interventions for disturbed motor control in NA and in other peripheral neurological disorders.

**Trial registration:**

ClinicalTrials.gov, NCT03441347. Registered on 20 February 2018.

**Electronic supplementary material:**

The online version of this article (10.1186/s13063-019-3556-4) contains supplementary material, which is available to authorized users.

## Background

Plasticity is a feature of the central motor system that allows change in the system organisation. It enables the development of new motor strategies in a changing environment, which can be advantageous when learning a new skill, or when recovering from injury by adapting with a compensatory strategy. When elements of the motor system are damaged, for example in neurological disorders, neuroplasticity enables patients to regain (part of their) motor function [1, 2]. However, the plasticity is maladaptive when changes in the central motor system are not beneficial to functioning. Maladaptive neuroplasticity can have detrimental consequences, resulting in impaired motor function. There are indications that maladaptive motor strategies can occur not only in central, but also in peripheral nervous system disorders [3–6].

Neuralgic amyotrophy (NA) is a peripheral nervous system disorder in which (mal)adaptive central neuroplasticity might be important. There are several indications from clinical experience that (mal)adaptive central neuroplasticity is involved in this disorder [7]. However, little is currently known about the central mechanisms in this peripheral nervous system disorder. NA is a distinct peripheral nervous system disorder of the brachial plexus, with a yearly incidence ratio of 1/1000 [7, 8]. It can also be described as an asymmetric, autoimmune inflammation of the brachial plexus and peripheral nerves. In the acute phase, the inflammation causes damage to the affected nerves, leading to the characteristic acute severe upper extremity pain, multifocal paresis (i.e. muscle weakness) with functional impairments, and patchy areas of sensory loss. The long thoracic nerve that innervates the serratus anterior muscle, is affected in about 70% of patients with NA [9]. In a substantial subset of patients (> 50%), weakness of the serratus anterior muscle in the acute phase leads to compensatory, abnormal positioning and movement patterns of the scapula in the chronic phase. These patients develop chronic musculoskeletal pain in the paretic and compensating muscles, which leads to residual complaints of decreased functional capability of the affected upper extremity [10]. Many patients additionally suffer from impairment of activities of daily living, fatigue and decreased participation in daily occupations [7, 10]. The abnormal posture and movement patterns of the scapula are referred to as scapular dyskinesia. The concept of persisting shoulder complaints in NA is that through its plasticity, the motor system adapts to retain motor control of the shoulder region by forming compensatory movement patterns in the acute phase. After the acute phase, most of the damaged nerves recover over time and with this recovery, the strength of affected muscles, including the stabilising serratus anterior muscle, can return. However, recovery often does not lead to improved function because of dysfunctional coordination and instability of the scapula. Although some patients with NA recover well after 2–3 years, recovery is complicated in many [7, 9–12]. Residual complaints in NA are strongly correlated with persisting scapular dyskinesia [10]. There is currently no proven effective causative treatment for NA [13] and the usual care given, mostly standard physical therapy, is ineffective and may even worsen complaints in more than half of patients with NA [10]. The fact that scapular dyskinesia persists even when the peripheral nerves and strength of the stabilising scapula muscle recover implies that other, cerebral factors may play a role in explaining the residual symptoms and variable recovery in patients with NA. We introduce the concept that peripheral nerve damage in NA may lead to adaptations in motor planning and representations that are compensatory in the acute phase, but lead to impaired and dysfunctional motor control in the chronic phase (see Fig. 1).

**Fig. 1 Fig1:**
[figure not shown]
Cerebral reorganisation and rehabilitation after peripheral dysfunction in neuralgic amyotrophy. Schematic presentation of the concept that peripheral nerve damage leads to adaptations in motor planning that are compensatory in the acute phase, but lead to impaired motor control in the chronic phase. Neuralgic amyotrophy (NA) is an acute autoimmune inflammation of the brachial plexus, characterised by acute severe upper extremity pain and multifocal paresis. Many patients with NA develop abnormal motor control of the scapular region, scapular dyskinesia, which persists even after peripheral nerve recovery. This suggests that persistent scapular dyskinesia in NA may result from maladaptive neuroplasticity. Rehabilitation focused on relearning motor control, targeting cerebral mechanisms, can improve scapular movement and positioning, indicating that the impaired motor planning can be restored. This figure includes images that are adapted from *Nervous system diagram* licensed under the Creative Commons Attribution-Share Alike 4.0 International license, authored by Jordi March i Nogué and William Crochot

This suggested involvement of maladaptive motor planning is illustrated by the promising results of specific rehabilitation after NA [14]. Through rehabilitation focused on relearning motor control, which thus targets cerebral mechanisms, patients with NA can relearn how to correctly position and move their shoulder and arm, which normalises scapular coordination and stability and improves functional capability of the upper extremity. A specific multidisciplinary and personalised rehabilitation programme, consisting of a visit to a specialised outpatient clinic that is followed by 8 sessions of physical and occupational therapy over a period of 16 weeks, has been developed at the Radboud University Medical Center (Radboudumc) in Nijmegen, the Netherlands. This programme combines relearning of motor control with self-management strategies. A clinical pilot study in eight participants showed that this rehabilitation programme can substantially relieve complaints and improve daily function at the level of activities, performance and participation. The programme was feasible, as all patients with NA were able to complete the entire programme. The number needed to treat was low, with 75% of the participants improving on the primary outcome measures [14].

Taken together, the available evidence strongly suggests that maladaptive motor planning plays a role in long-term symptoms and disability in NA. Indirect evidence includes the presence of persistent scapular dyskinesia despite peripheral nerve recovery and muscle strength, and the fact that rehabilitation focused on relearning motor control can normalise scapular movements and positioning. However, at this time, there is no direct evidence for (mal)adaptive cerebral neuroplasticity in NA. Despite the high incidence of NA (1/1000 a year) [8] and the presence of debilitating residual complaints [10], there are no randomised controlled trials (RCTs) investigating rehabilitation therapies targeting the residual complaints in NA. The NA-CONTROL study is an RCT designed to fill this gap; it compares the effect of a rehabilitation programme specifically designed for the residual complaints in this disorder to usual care in patients with NA. Additionally, the trial will combine clinical measures with measures derived to assess motor planning and representations in the central motor system, to provide mechanistic insights into how the rehabilitation programme could change central motor system plasticity.

## Objectives

### Primary objectives

The primary objective of this study is to determine the effect of a specific rehabilitation programme that combines relearning of motor control by targeting cerebral mechanisms with strategies to improve self-management, on functional capability of the upper extremity compared to usual care in patients with NA.

### Secondary objectives

#### The secondary objectives of this study are:

To evaluate whether this rehabilitation programme results in improvements in a range of domains, including but not limited to scapular dyskinesia, participation, quality of life and personal factors such as pain and fatigue, compared to usual care in patients with NA.To assess the longer term (17 weeks post treatment) effects of the rehabilitation programme on a variety of outcomes, including but not limited to functional capability of the upper extremity, participation, quality of life and personal factors such as pain and fatigue.To determine the effect of this rehabilitation programme on cortical motor planning and representations compared to usual care in patients with NA.

## Methods

### Study description

The NA-CONTROL study is the first RCT to investigate treatment for residual complaints in neuralgic amyotrophy. It additionally investigates a relatively unexplored concept (i.e. the role of (mal)adaptive cerebral neuroplasticity in a disorder of the peripheral nervous system) and employs techniques (including functional magnetic resonance imaging (MRI)) that have not yet been used to study the underlying cerebral mechanisms in NA. This study is conducted at the Donders Institute for Brain Cognition and Behaviour and the departments of Rehabilitation and Neurology of the Radboudumc in Nijmegen, the Netherlands.

The effect of a rehabilitation programme on functional capability and motor planning of the upper extremity will be compared to that of usual care in this two-arm, single-centre, open-label RCT. The intervention group will receive a specific 17-week multidisciplinary rehabilitation programme at the Radboudumc outpatient clinic, focused on relearning motor control and self-management (see “Intervention” for more information). The usual care group will first receive usual care for a 17-week period, before entering the rehabilitation programme.

Patients in both groups will be assessed in a single session at baseline. At the end of the baseline measurement, patients will be randomised into the intervention or usual care group (see “Randomisation” for more information). After the first 17 weeks of treatment (i.e. rehabilitation programme or usual care), both groups will be assessed in a second session (at 18 weeks post baseline). After this second assessment, the group that initially received usual care will then follow the specific rehabilitation programme. After completing the 17-week rehabilitation programme, the usual care group will be assessed a third time (at 36 weeks post baseline). All patients will be asked to fill out several questionnaires by e-mail 17 weeks after completing the rehabilitation programme. This follow up will be at either 36 weeks (intervention group) or 54 weeks (usual care group) post baseline. Figure 2 provides a flow chart of the study design.

**Fig. 2 Fig2:**
[figure not shown]
Flowchart of the study design: 50 neuralgic amyotrophy patients will be included. After the baseline measurement, participants are randomised into either the intervention group or the usual care group (1:1 ratio). After the first 17-week treatment period, both groups will undergo the first outcome measurement. The usual care group will then receive the 17-week rehabilitation program, after which they will undergo the second outcome measurement. Participants in both groups will complete a follow up from home 17 weeks after completing the rehabilitation program. Wks, weeks

#### Sub-study

The baseline measurements of all patients with NA who are assessed for the randomised controlled trial described in this publication (see Fig. 2) will be used for a sub-study. Patients with NA will be compared to 25 age-matched and sex-matched healthy controls in this sub-study. The healthy controls are assessed in a single session. The primary objective of this sub-study will be to determine if patients with NA have altered cerebral activity related to motor planning of their affected arm, compared to healthy controls and compared to their non-affected arm. This sub-study is important for the interpretation of the secondary objective (the effect of this rehabilitation programme on cortical motor planning and representations), to provide information about which cerebral changes from the rehabilitation programme are associated with functional impairments in NA.

### Study population

NA is more prevalent in men than in women, with an incidence ratio of 2:1, and can affect people of all ages. NA has an idiopathic form with a median age of onset around 40 years and a hereditary form with a median age of onset of about 28 years [7, 9]. Patients 18 years or older, with either form of NA can participate in the study.

#### Number of participants and sample size calculation

In total, 50 patients with NA will be recruited for participation in this study. The required sample size was calculated from the results from the pilot study on the effect of the rehabilitation programme [14]. The improvement in functional capability of the upper extremity measured with the Shoulder Rating Questionnaire, Dutch Language Version (SRQ-DLV) was used for this sample size calculation. With a conservative standardised effect size of 0.29 (improvement in SRQ-DLV [14]), power of 0.90 and two-tailed testing (α = 0.05), we calculated a required sample size of 42 patients. Assuming 20% dropout or non-compliance, we need to include 50 patients with NA.

The Radboudumc hosts the national referral centre and the only expert multidisciplinary outpatient clinic for patients with NA in the Netherlands. Each year around 400 new patients with NA are seen, most referred by Dutch neurologists or general physicians. Of these 400 patients, about 40% are estimated to be eligible for inclusion (see “Inclusion criteria”). We therefore expect to be able to recruit sufficient patients with NA for this study within the 2-year inclusion period.

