### Randomisation and blinding

Patients with NA will be randomly assigned to either the experimental intervention or to the usual care in a 1:1 ratio. Patients are randomized using a Good Clinical Practice (GCP)-compliant system (Castor Electronic Data Capture), which employs stratified, variable block randomisation. To prevent uneven distribution of certain characteristics across groups, randomisation will be stratified according to two factors: sex (male/female) and age (4 blocks: 18–30, 30–42, 42–54, > 54 years). Randomisation will be performed on site (at the Donders Institute for Brain Cognition and Behaviour, Centre for Cognitive Neuroimaging) after the participant has completed the baseline measurement (see Table 1).

Due to the project design, it is not possible to blind participants or the assessor. Participants will inevitably know whether they are receiving the rehabilitation programme or usual care. The assessor cannot be blinded either, for multiple reasons: all assessments are performed by a single assessor; as the number of assessments differs across groups, the assessor will know which participant belongs to which group; as the rehabilitation programme takes place at the assessor’s workplace facility, the assessor could be un-blinded on encountering a participant visiting the facility for treatment.

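### The required sample size of 42 cannot be reproduced from the printed inputs (effect size 0.29, power 0.90, two-sided 0.05), so either the power or the effect-size label is wrong as written

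*Protocol article*

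**What the plan says.** The section on number of participants and sample size calculation in the protocol article gives the inputs as "With a conservative standardised effect size of 0.29 (improvement in SRQ-DLV [14]), power of 0.90 and two-tailed testing" (α = 0.05) and concludes "we calculated a required sample size of 42 patients". It then adds an allowance: "Assuming 20% dropout or non-compliance, we need to include 50 patients with NA". It calls the effect size standardised but does not give its type (d, f or other), the SD it is scaled by, the test, or a correlation between baseline and follow-up.

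The design to which this applies is a two-arm parallel comparison: "Patients with NA will be randomly assigned to either the experimental intervention or to the usual care in a 1:1 ratio". Under Primary outcome, the endpoint is the SRQ-DLV change between baseline and the end of the intervention. Under Proposed analysis, group differences are assessed with generalised estimating equations, with baseline adjustment only where judged necessary. The effect size is referenced to the pilot, which the Background describes thus: "A clinical pilot study in eight participants showed that this rehabilitation programme can substantially relieve complaints".

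**The concern.** A standardised effect of 0.29 is small, and small effects need hundreds of patients per arm. A total of 42 at 90% power is out of line with that by a factor of about twelve, too much for rounding or a different approximation. This paragraph is the article's only justification of the trial's size, and it concerns the primary outcome. A reader who takes it at face value will believe that the trial can reliably detect a difference of 0.29 SD, and could misread a non-significant result accordingly.

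**Working it through.** **Inputs.** Effect size 0.29, power 0.90, two-sided α = 0.05, 42 before loss, 20% loss and 50 to include, all from the sample size section; 1:1 allocation from Randomisation and blinding. At 1:1, 42 is 21 per arm.

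**1. 0.29 as a standardised mean difference (d).** Per arm, n = 2(z₀.₉₇₅ + z₀.₉₀)²/d² = 2(1.960 + 1.282)²/0.29² = 249.9, so 250. The non-central t gives 251 (power 0.899 at 250, 0.900 at 251), or 502 in total. The plan's 42 is not reproduced.

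**2. Power at the planned size if d = 0.29.** Non-central t with non-centrality d√(n/2) and 2n − 2 degrees of freedom:

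| n per arm | non-centrality | power |
|---|---|---|
| 20 | 0.917 | 14.5% |
| 21 | 0.940 | 15.1% |
| 25 | 1.025 | 17.1% |

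**3. Other routes with 0.29 as a mean difference.** A one-sided two-sample test needs 205 per arm, and 80% power two-sided needs 188 per arm. A paired test in one group needs 127. If 0.29 is scaled by the raw-score SD and the analysis adjusts for baseline, the residual SD is √(1 − ρ²), by normal approximation:

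| ρ | n per arm for 90% | power with 21 per arm |
|---|---|---|
| 0.5 | 188 | 19% |
| 0.7 | 128 | 26% |
| 0.9 | 48 | 58% |
| 0.95 | 25 | 85% |
| 0.96 | 20 | 92% |

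So 21 per arm suffice only at a correlation of about 0.96.

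**4. Other metrics (totals at 90% power).** One-way ANOVA with f = 0.29 gives 128, r = 0.29 gives 117, f² = 0.29 gives 39, and η² = 0.29 gives 28.

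**5. 0.29 as Cohen's f for a group-by-time interaction.** With two groups and m time points, λ = f²·N·m/(1 − ρ), on m − 1 and (N − 2)(m − 1) degrees of freedom.
- m = 2, ρ = 0.36: λ = 0.0841 × 42 × 2/0.64 = 11.04, and power on F(1, 40) is 0.900. This reproduces 42.
- m = 2, ρ = 0.50: 34 patients give 90%. Here 42 patients give 95.6%, so 42 is the answer for 95% power, which is not the stated 0.90.
- m = 3, ρ = 0.20: 42 patients give 90.2%.

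**6. What f = 0.29 means as a difference (m = 2).** The between-group difference in change is 4f = 4 × 0.29 = 1.16 raw SD, and the SD of change is √(2(1 − ρ)) raw SD. At ρ = 0.36 the ratio is 1.16/√1.28 = 1.03 SD of change. At ρ = 0.50 it is 1.16/1 = 1.16.

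**7. What the design can detect.** The loss step matters here: 50 × 0.8 = 40, or 20 per arm, whereas retaining 42 would need 42/0.8 = 52.5, so 53. Detectable between-group difference in SD of change, non-central t:

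| n per arm | 90% power | 80% power |
|---|---|---|
| 20 | 1.05 | 0.91 |
| 21 | 1.03 | 0.89 |
| 25 | 0.94 | 0.81 |

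**The case against.** The strongest reply is that the article never says 0.29 is a mean difference. A group-by-time calculation with Cohen's f is a standard choice for a two-group pre/post trial. It fits a change endpoint and a repeated-measures analysis, and it yields 42 at 90% power for plausible correlations. This stands. A reader might infer that the trial simply has 15% power for its design effect; the document does not support that without the condition that 0.29 is d on the SD of change. Nor can one say that only a correlation of 0.36 gives 42, since three time points and a correlation of 0.20 also do. None of these routes is shown to be the one the authors took.

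The reply does not rescue the paragraph. On the two-time-point reading the target is a difference of about 1 SD of change or more, and a reader given 0.29 as a cautious standardised effect could not know that.

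Two further inferences go too far. One is that improvement under usual care must shrink the pilot effect: the Background says usual care is ineffective and may worsen complaints in over half of patients, so the contrast could move either way. The other is that the pilot had no control group: the article describes none, but it does not set out the pilot's design, and how 0.29 was derived from it cannot be checked here.

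That a statistical analysis plan will follow is no answer, because the point concerns printed figures that do not follow from one another.

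**Conclusion.** The point holds in conditional form. The total of 42 does not follow from the inputs as printed. If 0.29 is a standardised mean difference, the stated power is wrong: the requirement is 502, about twelve times the stated figure, and power with 20 to 25 per arm is 14.5% to 17%. If 0.29 is an interaction f with two time points, the power can be right, but the label misleads, because the trial is then sized for a difference of about 1 SD of change. One of the two must be corrected.

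The t-based results assume equal variances, 1:1 allocation and an unadjusted comparison of change. Strong baseline adjustment would raise power, but with 0.29 on the raw-score SD it reaches 90% at 21 per arm only if the correlation is about 0.96.

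**What to change.** Rewrite the paragraph and keep the sample size.

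1. Name the effect-size metric, the test, the SD and the assumed correlation (and number of time points, if relevant) actually used to obtain 42.
2. Replace the power statement with what the design delivers, for example: with the 20 patients per arm expected after 20% loss from 50, the trial has 90% (80%) power for a between-group difference of 1.05 (0.91) SD of change in SRQ-DLV; with 21 per arm, 1.03 (0.89).
3. Stop presenting 0.29 as a conservative standardised effect unless the metric is given beside it together with the equivalent between-group difference.
4. Say that 0.29 derives from improvement in a pilot of eight participants and is not a stated difference versus usual care.

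Reading a non-significant result through its confidence interval would be sensible, but that is a reporting preference and not part of the correction. The cost is one reworded paragraph and a less favourable power claim. No extra patients are needed.

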#### Usual care (control group)

The 25 patients with NA in the control group will receive usual care for 17 weeks. The usual care may vary for each individual, and may even consist of no treatment at all. Patients are asked to keep a diary during this period, in which they will report on the care/treatment they receive, including the type of care (e.g. physical or occupational therapy, acupuncture), number of sessions and composition of the care (e.g. strength training, aerobic training, massage). After 17 weeks, patients in the usual care group will start with the 17-week rehabilitation programme at the Radboudumc as described above.

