### Statistics and data analysis

#### Proposed analysis

All continuous variables will be summarised as the number of (missing) observations, mean, standard deviation, median and range. Categorical variables will be summarised as the number of (missing) observations and number and percentage in each category. This will be done separately for each time point (baseline, outcome measurement(s) and follow up) and for the change from baseline for each intervention group.

The primary clinical outcome (SRQ-DLV score) and most other clinical outcomes are linear or quasi-linear. Group differences in the effects of the intervention on primary and secondary outcome measures and the influence of possible effect modifiers will be investigated using generalised estimated equations analysis. If necessary, analyses will be adjusted for group differences in functional capability of the upper extremity (SRQ-DLV score), age and sex at baseline. Data will be analysed according to the intention-to-treat principle. Data will be appropriately transformed if necessary, to satisfy modelling assumptions. Prior to locking of the data, a statistical analysis plan will be drawn up and approved by a statistician and the principal investigator.

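### Fifty patients leave 40, not the required 42, after the assumed 20% loss, and a headcount allowance does not properly cover non-compliers who stay in the intention-to-treat analysis

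*Protocol article*

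**What the plan says.** The section on number of participants and sample size calculation starts from "With a conservative standardised effect size of 0.29", with 90% power and a two-sided 5% test, and concludes: "we calculated a required sample size of 42 patients". It then adds the allowance for losses: "Assuming 20% dropout or non-compliance, we need to include 50 patients with NA". The same section fixes the recruitment target: "In total, 50 patients with NA will be recruited for participation in this study". Under Randomisation and blinding, patients are "randomly assigned to either the experimental intervention or to the usual care in a 1:1 ratio", and the usual care section puts 25 patients in the control group.

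On the analysis, the Proposed analysis section says: "Data will be analysed according to the intention-to-treat principle". Under Withdrawal procedures, a patient who withdraws is not assessed again, but data already collected are used. The article names no per-protocol analysis. It does not define non-compliance or say how the 20% divides between dropout and non-compliance.

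**The concern.** There are two separate problems in one sentence.

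The first is arithmetic. An allowance for loss should leave the required number once the assumed loss has happened. Here it does not: at the plan's own loss rate, the trial ends below its own requirement. A reader would take from the sentence that 20% loss is covered, when only 16% is.

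The second is the kind of allowance. Dropout and non-compliance are put into one headcount inflation, but they act differently. A patient with no 18-week assessment reduces the number analysed. A non-complier who attends that assessment stays in the intention-to-treat comparison and reduces the average difference between the arms. Required sample size grows with 1/(1 − c) for a lost share c, but with 1/(1 − c)² for a retained share c that gains nothing. One headcount factor therefore does not cover both.

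At stake is the accuracy of the stated power and of the stated tolerance for loss.

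**Working it through.** **Inputs from the sample size section:** 42 required; 20% dropout or non-compliance; 50 to include; power 0.90; two-sided α of 0.05. Allocation is 1:1. I take 42 as given.

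**Reproducing the 50.** Multiplying by one plus the loss rate gives 42 × 1.20 = 50.4, which matches the stated 50 when rounded down. This is the likely route, although the article does not show it.

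**The correct inflation.** Divide by the share retained: 42 / (1 − 0.20) = 52.5, so 53 patients, or 54 for equal arms.

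**Back-check.**
- 50 × 0.80 = 40 evaluable patients, 20 per arm, which is 2 short of 42.
- Largest loss that still leaves 42: 1 − 42/50 = 0.16, or 16%.

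**Cost in power if all 20% are lost.** The article gives a standardised effect of 0.29 without naming its type, and it does not name the model behind the 42. For illustration I assume a two-sample t-test and solve for the standardised difference d that gives 90% power at 21 per arm. By the non-central t distribution, d = 1.025. This is an assumption, not a figure from the article.
- 21 per arm, d = 1.025: power 90.0%.
- 20 per arm, d = 1.025: power 88.5%.

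The loss is about 1.5 percentage points.

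**Effect of retained non-compliers, on the same assumed d.** If a share c of patients stays in the analysis and keeps a fraction r of the benefit, the effect becomes d × [1 − c(1 − r)].

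| Assumed use of the 20% | Analysed per arm | Effect multiplier | Power |
|---|---|---|---|
| All lost | 20 | 1.00 | 88.5% |
| 10% lost, 10% retained with no benefit | 22.5 | 0.90 | about 86% |
| All retained, no benefit (r = 0) | 25 | 0.80 | 81.1% |
| All retained, 60% of benefit (r = 0.6) | 25 | 1 − 0.20 × 0.40 = 0.92 | 90.4% |

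The r = 0 row with all 20% retained would need about 42/0.80² = 65.6, so 66 patients, for 90% power.

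**The case against.** The strongest reply is that the proven shortfall is two patients and about 1.5 points of power, that no conclusion of the trial turns on it, and that 20% may be cautious. The Background reports that all eight pilot participants completed the programme, and 50 patients still deliver 42 at up to 16% loss. The point about size stands: this is a correction to a statement and not a flaw in the design. The pilot is thin support, being eight patients who all received the programme; it says nothing about retention under usual care.

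It can also be said that generalised estimating equations use partial data, so dropouts are not wholly lost. But a patient who withdraws before 18 weeks is not assessed again and contributes no observed change in the primary outcome. The Missing data section provides for imputation only where needed and feasible. The plan itself inflates its number because it expects such patients to be lost.

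On the second part, a reader might infer that non-compliers can never be counted as losses. The article does not support that. Non-compliance is undefined and may include patients who miss the 18-week assessment, who are losses under any analysis principle. How such patients are classified is commonly settled in the statistical analysis plan, which the article says will be written. The dilution point holds only for non-compliers who attend the assessment, and their number is not given.

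A reader might also infer that the trial has only 81% power, or needs 66 patients. That requires three things the article does not say: a d of about 1.03, all 20% being retained non-compliers, and no benefit in any of them. It is the worst end of an assumed range.

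**Conclusion.** The arithmetic error is certain and needs no outside assumption: 42 required, 20% loss and 50 included cannot all stand together. Fifty leaves 40 after 20% loss and covers 16%; 53 patients, or 54 in equal arms, would be needed to keep 42.

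Its cost, if all the loss is dropout, is about 88.5% power against 90%. That figure rests on the back-solved d and the two-sample model.

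The non-compliance point holds in a limited form. Non-compliers who are assessed at 18 weeks dilute the intention-to-treat effect, and a headcount allowance does not properly cover them. If the whole 20% is of this kind, power with 50 analysed lies between about 81% and about 90% as the benefit they keep goes from none to about 60%. The article does not allow a narrower statement. Whether 42 itself follows from the stated effect size of 0.29 is a separate question that this point leaves open.

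**What to change.** Replace the allowance sentence with one that says: fifty patients allow for 16% loss to follow-up; with 20% loss, 40 evaluable patients remain. Give the power at 40 under the model and effect size that produced the 42, in place of the illustrative d used here. Limit the allowance to patients without an outcome assessment, and add that non-compliers who are assessed remain in the intention-to-treat analysis and would dilute the effect.

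The restatement costs a sentence or two and makes the stated tolerance slightly less favourable. It needs no extra enrolment and no change to design or treatment. Putting a number on the dilution would take more: an assumed share of retained non-compliers and an assumed residual benefit, neither of which the article gives. If the team wants that number, it should be shown as a range. Because the statistical analysis plan is to be approved before the data are locked, the corrected statement can also be placed there.
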